### Adverse events

3.7

In accordance with International Conference on Harmonization (ICH) Good Clinical Practice guidelines, a serious adverse event (SAE) is defined as any untoward medical occurrence that results in death, is life-threatening, requires inpatient hospitalization or prolongation of existing hospitalization, results in persistent or significant disability/incapacity, or leads to a congenital anomaly or birth defect. Any other medically significant event that may jeopardize the patient, or may require medical or surgical intervention to prevent one of these outcomes, will also be classified as an SAE.

Patient safety will be closely monitored throughout the study. Safety assessments will include routine physical examinations, monitoring of vital signs, laboratory tests, and 12-lead electrocardiograms (ECGs). All adverse events (AEs), regardless of severity, duration, or suspected relationship to study intervention, will be systematically documented in the electronic case report form (eCRF), reviewed by the investigator, and followed until resolution or stabilization. All SAEs will be reported promptly to the Ethics Committee in compliance with regulatory requirements and institutional policies. The Data and Safety Monitoring Board (DSMB), where applicable, will periodically review safety data to ensure ongoing participant protection.

### Statistical analysis

3.8

All analyses will be performed using SPSS version 25.0 and R. Continuous variables will be checked for normality with the Kolmogorov–Smirnov test and summarized as mean ± SD or as median (interquartile range) if not normally distributed. Between-group comparisons will use analysis of variance (ANOVA) or Kruskal–Wallis tests as appropriate, while categorical variables will be expressed as counts and percentages and compared with chi-square or Fisher’s exact tests. The primary endpoint, ALSFRS-R slope from baseline to 12 months, will be analyzed using a mixed-effects model for repeated measures including group, time, and group × time interaction, with baseline score as covariate and unstructured covariance for within-subject correlation. Secondary outcomes such as muscle strength, spasticity, respiratory function, and quality of life will be analyzed with similar mixed-effects approaches, supplemented by post-hoc tests with Bonferroni correction when necessary. For the imaging substudy, changes in SV2A PET SUVR values will be analyzed using the same mixed-effects framework, with multiplicity controlled across primary regions of interest. Correlations between imaging and clinical outcomes will be examined using Pearson or Spearman coefficients depending on distribution. Analyses will follow the intention-to-treat principle, with missing data handled using maximum likelihood estimation under a missing-at-random assumption, and sensitivity analyses performed to test robustness. A two-sided *p* value <0.05 will be considered statistically significant for primary analyses.

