### Study design

3.1

This study is designed as a prospective, parallel-group, randomized controlled trial with a three-arm comparative design. Patients with ALS are identified and enrolled through systematic screening at the Hubei Provincial Hospital of Traditional Chinese Medicine. Recruitment began in September 2024 and is ongoing. Eligible participants will be randomly assigned in a 1:1:1 ratio to one of three groups: (i) Tuina therapy combined with Riluzole, (ii) sham Tuina therapy combined with Riluzole, or (iii) Riluzole alone. Randomization is performed using a computer-generated sequence created by an independent statistician not involved in participant recruitment or outcome assessment. Allocation is concealed using sequentially numbered, opaque, sealed envelopes (SNOSE) prepared prior to enrollment, and the envelopes are opened only after completion of baseline assessments to minimize selection bias.

All participants continue to receive standard pharmacological treatment with oral Riluzole throughout the trial. The intervention group receives a structured program of Tuina therapy, while the control group receives sham Tuina matched in duration and frequency. The standard care group receives Riluzole only. Interventions are delivered over a total treatment period of 12 months, beginning with a 4-week intensive phase followed by a maintenance schedule. Clinical efficacy and safety outcomes are assessed at baseline, after the 4-week intensive phase, and at Months 6, 12, 18, and 24. A mechanistic substudy employs presynaptic SV2A PET imaging at baseline and Month 6 to explore synaptic integrity changes associated with Tuina. A schematic flowchart is presented in Figure 1, and the study timeline is summarized in Table 1.

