### Sample size

3.2

The sample size calculation was primarily based on the ALSFRS-R as the main clinical endpoint, reflecting the study’s primary objective to evaluate functional decline. Calculations were performed using G*Power software (version 3.1.9.7) for an F-test. Based on a projected medium effect size (*f* = 0.35) for the ALSFRS-R, derived from prior research and clinical expectations for interventions in ALS, a statistical power of 90% (1-*β* = 0.9) and a significance level of *α* = 0.05 across three groups, a total sample size of 108 participants was determined to be necessary. This calculation yields an actual power of approximately 0.905, ensuring sufficient power to detect a clinically meaningful effect on the primary outcome.

To account for the inherent heterogeneity of ALS and to enhance the ability to detect moderate effect sizes and explore potential subgroup differences, the final recruitment target has been further adjusted. Considering an anticipated dropout rate of approximately 20% over the 12-month treatment and follow-up period, the required effective sample size of 36 participants per group (108 participants total) necessitates recruiting 45 participants per group. Thus, the total recruitment target for the study is 135 participants (45 participants × 3 groups). This increased recruitment target ensures that, even with expected attrition, the study will retain sufficient power for the primary outcome and will also allow for more reliable detection of moderate effect sizes, thereby enhancing the precision of exploratory subgroup analyses in this complex disease.

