### Eligibility criteria

3.3

To ensure a homogeneous sample regarding initial disease severity and to minimize the impact of disease heterogeneity, stringent eligibility criteria will be applied, drawing inspiration from successful ALS clinical trials. This approach aims to create a cohort with comparable disease progression rates and functional status at baseline, thereby enhancing the internal validity and interpretability of our findings. Participants will be eligible for enrollment if they meet all the following criteria: Participants must have a confirmed diagnosis of definite or laboratory-supported probable ALS according to the revised El Escorial criteria, including both sporadic and familial cases.

Eligible individuals will be between 18 and 80 years of age, regardless of sex, and will be enrolled only if they are within 24 months of symptom onset, a criterion intended to reduce variability in disease progression rates. Participants must present with mild to moderate disability corresponding to Sinaki–Mulder stages I–III. Additionally, at baseline, they will need to have a total ALSFRS-R score between 30 and 40, with a minimum score of ≥2 on each of the 12 individual items; this combined threshold is designed to capture patients with early to moderate disability, avoiding floor or ceiling effects and ensuring the scale’s sensitivity to change. Participants must have a forced vital capacity (FVC) of at least 50% of the predicted value based on age, sex, and height, and specifically an FVC of ≥80% of predicted values. Eligible individuals should demonstrate residual limb muscle strength of grade 3 or higher on the Medical Research Council (MRC) scale. Furthermore, patients will be classified using King’s ALS clinical stages 1–2 to confirm early functional stages based on clinical evaluation.

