### Outcome measurement

3.6

Each participant will undergo assessments at baseline (T0), immediately after the 4-week intervention, and at follow-up visits scheduled at 6, 12, 18, and 24 months. These repeated measures are designed to capture both short-term effects of the intervention and its longer-term influence on disease progression, functional capacity, and quality of life. The primary outcome is the change in global functional status, measured using the Amyotrophic Lateral Sclerosis Functional Rating Scale–Revised (ALSFRS-R) (8). The ALSFRS-R is a validated, widely used instrument that evaluates functional impairment across bulbar, motor, and respiratory domains. Changes in ALSFRS-R scores from baseline to each assessment point will be analyzed, with the primary comparison defined as the slope of decline from baseline to 12 months between the intervention groups.

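### The primary slope model names baseline ALSFRS-R as a covariate without a baseline × time term, so the slope comparison goes essentially unadjusted for baseline

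*Protocol article*

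**What the plan says.** The Outcome measurement section (3.6) analyses ALSFRS-R change, "with the primary comparison defined as the slope of decline from baseline to 12 months between the intervention groups". The Statistical analysis section (3.8) repeats the slope endpoint and specifies a "mixed-effects model for repeated measures including group, time, and group × time interaction", "with baseline score as covariate and unstructured covariance for within-subject correlation". Group × time is the only interaction listed.

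Three other statements bear on the point:
- Visits: outcomes are "assessed at baseline, after the 4-week intensive phase, and at Months 6, 12, 18, and 24" (Study design, 3.1).
- Missing data: "missing data handled using maximum likelihood estimation under a missing-at-random assumption" (3.8).
- Entry range: "a total ALSFRS-R score between 30 and 40" (Eligibility criteria, 3.3).

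Section 3.8 does not say whether time is continuous or categorical, or whether the baseline score also belongs to the response vector.

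**The concern.** When the endpoint is a slope, the treatment effect is the group × time term. A baseline covariate is constant within a participant. Entered as a main effect, it raises or lowers the whole trajectory and says nothing about its steepness. The plan evidently means to allow for baseline severity, yet the terms it lists do not do so on the comparison that decides the trial.

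If baseline severity predicts later decline, two things are lost. The slope contrast keeps variance that baseline could have explained, and a chance difference in baseline severity between arms is not corrected.

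**Working it through.** **1. The plan's own figures.** For a one-way F-test with "Based on a projected medium effect size (*f* = 0.35) for the ALSFRS-R", three groups and α = 0.05, λ = N·f² = 108 × 0.1225 = 13.23 on 2 and 105 degrees of freedom. Power is 0.9047, which agrees with the stated 0.905. Dropout: 36/(1 − 0.2) = 45 per arm, 135 in all. Both reproduce, and neither uses a baseline covariate.

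**2. Algebra.** Write the listed model as Y_ij = μ(t_j) + γ_g + δ_g(t_j) + β·B_i + e_ij. In any within-participant time contrast, for example Y_i,12 − Y_i,1, the term β·B_i cancels. The contrast equations then hold only intercept and group terms, a subset of the regressors in the level equation. Generalised least squares therefore makes no use of B_i in estimating them, whatever the covariance matrix. This holds for linear and for categorical time.

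**3. Numerical illustration.** One simulated data set, 3 × 36, visits at months 1, 6 and 12, unstructured covariance, maximum likelihood. All inputs are assumed: baseline uniform on 30 to 40 with deliberate arm shifts of +1.2 and −0.8; slope −1.0 per month plus 0.08 per baseline point; residual slope SD 0.45; error SD 1.3. Entries are the two contrasts against the reference arm, with SE in brackets.

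| Complete data | No baseline term | Baseline main effect | Baseline and baseline × time |
|---|---|---|---|
| Group × time, month 12 vs week 4 | 3.973 / −0.468 (1.347 both) | 3.973 / −0.468 (1.347 both) | 2.249 / 0.264 (1.305 / 1.254) |
| Linear slope per month | 0.3625 / −0.0485 (0.1224 both) | 0.3625 / −0.0485 (0.1224 both) | 0.2059 / 0.0180 (0.1185 / 0.1139) |
| Month-12 visit contrast | 6.79 / −1.34 | 4.50 / −0.37 | 2.76 / 0.37 |

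The main effect leaves both slope rows untouched and alters only the single-visit row. Placing the baseline score in the response vector, under arbitrary covariance matrices, gave the same identity for group × time.

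With about 20% missing at random at month 12, the group × time estimates were 3.829 / −0.404 (no baseline), 4.013 / −0.151 (main effect) and 2.450 / 0.188 (baseline × time). The main effect thus moved them by 0.184 and about 0.25, against SEs of 1.402 and 1.446, that is 0.13 and 0.17 SE. The first shift was away from the baseline × time fit and the second towards it.

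**4. Size.** The documents give no SDs and no baseline–slope correlation r. Assume true baseline SD 2.5, slope SD 0.6 points/month and error SD 1. For visits at 0.92, 6 and 12 months the sum of squares of time about its mean is 61.5. The share of slope variance that baseline × time removes is

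ρ² = (r × 2.5 × 0.6)² / [(2.5² + 1)(0.6² + 1/61.5)] = (1.5r)² / 2.728.

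| r | ρ² | Equivalent extra participants, 1/(1 − ρ²) − 1 | Power with λ = 13.23/(1 − ρ²) | Slope difference per 1-point baseline imbalance, 12 × 1.5r/7.25 |
|---|---|---|---|---|
| 0 | 0 | 0 | 0.905 | 0 |
| 0.2 | 3.3% | 3% | 0.914 | 0.50 points/year |
| 0.3 | 7.4% | 8% | 0.926 | 0.74 points/year |
| 0.4 | 13.2% | 15% | 0.941 | 0.99 points/year |

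If the fitted slope also uses the baseline visit (0, 0.92, 6, 12 months; sum of squares 91.35), shared baseline error lowers the shares to about 2%, 6% and 11%. The range is therefore 2% to 13%. The SD of a chance difference in mean baseline between two arms of 45 is √(2 × 7.25/45) = 0.57 points.

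**The case against.** **Reading.** The article says covariate, not main effect only, and a full analysis plan that is not shown could add the interaction. That is fair as a limit. But the article does list the model's terms and names an interaction for group and none for baseline. A statistician following the text would fit a main effect.

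**Contrast.** If change from baseline is the response, the baseline-to-month-12 group difference is a single-visit contrast, which the main effect does adjust (6.79 to 4.50 in the illustration). This is correct, but the declared comparison is a slope, so the adjustment falls on a different quantity.

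**Stronger readings that the documents do not support.**
- A reader might infer that the primary comparison is biased. It is not: allocation is random, and chance baseline imbalance is ordinary sampling error already reflected in the standard error.
- A reader might infer that the trial is underpowered. The 0.905 uses no covariate, so adjustment would add to it and its absence takes nothing away.
- A reader might take the equality as exact in practice. With the planned dropout it is only approximate.
- A reader might extend the point to every secondary outcome and covariate. The article does not define the secondary outcomes other than ALSFRS-R trajectory as slopes, and a main effect adjusts their visit contrasts.

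**Size.** The gain rests wholly on an assumed correlation, and the narrow entry range may keep it modest. This stands.

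**Conclusion.** The point holds as a matter of efficiency, not validity. With the terms listed in section 3.8, naming baseline as a covariate does essentially nothing for the declared primary comparison. The identity for complete data is algebraic and depends on no assumption beyond reading the covariate as a main effect. The size does depend on assumptions: for baseline–slope correlations of 0.2 to 0.4 and the SDs given above, 2% to 13% of the variance of the slope contrast, and nothing if the correlation is zero. The simulated estimates only illustrate the identity; their imposed imbalance makes the differences larger than chance would usually produce.

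**What to change.** In section 3.8, for the primary slope analysis, replace the baseline clause with: *with baseline score and baseline score × time as covariates* (baseline × visit if time is categorical). State that the response is the post-baseline scores or the change from baseline. Use the same form for a secondary outcome, or for another covariate such as site of onset, only where the tested effect is itself a slope (group × time).

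The cost is one line of wording and one degree of freedom with linear time, or two with three categorical post-baseline visits. No new data are needed, and 108 and 135 stay as they are. The change should be fixed before unblinding, since adding the term afterwards would be a data-driven choice on the primary test.

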## Objectives and hypothesis

2

Given the rapidly progressive nature of ALS and the limited benefits of current pharmacological interventions, there is an urgent need for adjunctive strategies that may preserve function and improve patient quality of life. Tuina has been proposed as a supportive intervention that may influence neuromuscular performance and central neural function.

The primary objective of this trial is to evaluate whether Tuina therapy combined with Riluzole can slow the decline of physical function in patients with early-stage ALS, as assessed by changes in the ALSFRS-R. Secondary objectives include determining the impact of the combined intervention on respiratory capacity, muscle strength, spasticity, and quality of life, as well as assessing the overall safety and tolerability of repeated Tuina sessions. Beyond clinical outcomes, the trial will also explore potential neurobiological mechanisms of Tuina. Using presynaptic SV2A PET imaging at baseline and 6 months, the objective is to examine whether functional changes are accompanied by preservation or enhancement of synaptic integrity in motor system regions.

It is hypothesize that Tuina combined with Riluzole will significantly slow functional decline and improve quality of life compared with Riluzole alone or sham Tuina plus Riluzole. Furthermore, it is anticipated that these clinical benefits may be linked to measurable synaptic changes, providing mechanistic evidence for Tuina as a complementary therapy in ALS.

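### Bonferroni for the secondary-outcome post-hoc tests is valid but needlessly conservative: Holm, or a closed three-arm test where there is one contrast per arm pair, gives more power at the same familywise level

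*Protocol article*

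**What the plan says.** The trial has three arms (Protocol article, 3.1 Study design): "Eligible participants will be randomly assigned in a 1:1:1 ratio to one of three groups". The hypothesis in section 2 sets Tuina plus Riluzole against each control, "compared with Riluzole alone or sham Tuina plus Riluzole", so conclusions rest on pairwise contrasts.

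Section 3.8 gives the secondary outcomes (muscle strength, spasticity, respiratory function, quality of life) mixed models like the primary one, "supplemented by post-hoc tests with Bonferroni correction when necessary". It does not say whether the corrected family is the three arm pairs, the visits, the outcomes or a mixture. It does not say whether an overall test must be significant first.

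The primary endpoint, the ALSFRS-R slope to 12 months, has a group × time model and this criterion: "A two-sided *p* value <0.05 will be considered statistically significant for primary analyses". No Bonferroni correction is attached to it. Section 3.2 sizes the trial on an overall three-group F-test with "a significance level of *α* = 0.05 across three groups".

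**The concern.** Bonferroni tests every member of a family of m comparisons at 0.05/m, however many of the others have been rejected. Holm uses 0.05/m only for the smallest p-value and then relaxes to 0.05/(m−1), and so on up to 0.05. It has the same familywise guarantee under the same conditions and can never reject less. The clause therefore gives up some power for nothing but simplicity.

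With exactly three arms and one contrast per pair, more can be recovered. If any two of the three pairwise nulls are true, all three means are equal. By the closure principle, a 5% overall test followed by unadjusted 5% pairwise tests then controls the familywise error strongly for that outcome.

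At stake is the chance of separating Tuina from one or both controls on secondary outcomes, with about 36 evaluable participants per arm.

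**Working it through.** **Inputs from section 3.2.** "Based on a projected medium effect size (*f* = 0.35) for the ALSFRS-R"; three groups; α = 0.05; "a total sample size of 108 participants was determined to be necessary", which is 36 per arm; "This calculation yields an actual power of approximately 0.905".

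**Reproducing the plan's figure.** Noncentral F with 2 and 105 df and λ = N·f² = 108 × 0.35² = 13.23 gives power 0.9047. N = 105 gives 0.896, so 108 is the smallest balanced total reaching 0.90. For dropout, 36/(1 − 0.20) = 45 per arm and 3 × 45 = 135. All of this agrees with the plan. The calculation is for the primary endpoint's overall test and contains no Bonferroni step.

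**Turning f into pairwise differences (the pattern of means is an assumption).**
- One arm differs, means (d, 0, 0): f = d·√2/3, so d = 0.35 × 3/√2 = 0.742 SD.
- Evenly spaced means (D, D/2, 0): f = D/√6, so D = 0.35 × √6 = 0.857 SD, with adjacent gaps of 0.429 SD.

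**Direct check of Bonferroni.** One pair, 36 per arm, 105 error df, noncentrality 0.742 × √(36/2) = 3.15. Power is 0.762 at α = 0.05/3 = 0.0167, against 0.877 at an unadjusted, ungated 0.05.

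**Comparing procedures.** 400,000 simulated three-arm data sets per case, 36 per arm, pooled variance, one contrast per pair. Closed means the overall F-test at 0.05, then pairs at 0.05.

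| Means (SD units) | Quantity | Bonferroni | Holm | Closed |
|---|---|---|---|---|
| (0.742, 0, 0) | power, one Tuina contrast | 0.76 | 0.79 | 0.85 |
| (0.742, 0, 0) | power, both Tuina contrasts | 0.64 | 0.70 | 0.79 |
| (0.857, 0.429, 0) | power, largest pair | 0.884 | 0.888 | 0.902 |
| (0.857, 0.429, 0) | power, each adjacent pair | 0.275 | 0.354 | 0.434 |
| (0, 0, 0) | familywise error | 0.043 | 0.043 | 0.050 |
| (0.742, 0, 0) | error on the null pair | 0.017 | 0.036 | 0.050 |
| (3, 0, 0) | error on the null pair | 0.017 | 0.050 | 0.050 |

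With one arm differing, closed testing gains 0.85 − 0.76 = 9 points for one contrast and 0.793 − 0.637, about 16 points, for both. With evenly spaced means it gains 0.902 − 0.884, about 2 points, for the largest pair and 0.434 − 0.275, about 16 points, for adjacent pairs. At a smaller difference of d = 0.5 (one arm differing), one contrast has 38% power with Bonferroni and 48% closed; both contrasts have 23% and 39%.

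**Where the shortcut fails.**
- Without the gate, unadjusted pairwise tests have familywise error 0.121 when all arms are equal.
- If a significant multi-visit group × time test is followed by unadjusted pairwise tests at every visit, and some effect is real, familywise error is 0.10 to 0.24 with three visits and 0.13 to 0.36 with five. This comes from 60,000 runs per case with assumed within-subject correlation 0.5 to 0.8. The trial has five post-baseline visits, three of them by month 12.

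**The case against.** Bonferroni is valid, and the article names neither the family nor a gate; such detail often sits in an analysis plan, which is not shown here. If the family runs over visits or outcomes, the three-arm closure argument does not apply. This stands. It is why Holm is the general remedy, since it needs no knowledge of the family, and why closed testing is offered only for one contrast per pair.

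A reader might infer that Bonferroni after a three-arm test pays twice for multiplicity and protects nothing. The documents do not support that. No gate is stated, and without one the correction is the only protection. If a gate is present, adding it to Bonferroni leaves power almost unchanged (0.761 against 0.760 for one contrast). Bonferroni also holds the error on a truly null pair at 1.7%, where closed testing allows 5%. And a significant group × time test over several visits does not license unadjusted visit-wise tests.

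The effect size used is projected for the ALSFRS-R. The article gives none for the secondary outcomes, so the power figures are illustrations. Nor does the hypothesis cover every secondary outcome: section 2 names functional decline and quality of life.

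**Conclusion.** The Bonferroni clause is correct but less efficient than alternatives with the same familywise level. Holm's advantage holds for any family. The further gain from closed testing holds only with three arms, one pre-named contrast per pair and a pre-stated overall gate.

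For one arm differing by 0.74 SD with 36 per arm, Holm adds about 3 points for one Tuina contrast and 6 for both; closed testing adds about 9 and 16. With evenly spaced means the closed gain ranges from about 2 to 16 points. These sizes assume the stated mean patterns, equal variances and an effect borrowed from the primary endpoint.

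A reader might infer that the trial's 90% power is eroded. It is not: the clause is attached to secondary outcomes, and the sample size rests on the uncorrected overall F-test. This is an optional improvement; nothing in the plan is invalidated by leaving the clause as it is.

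**What to change.** In section 3.8, or in the analysis plan, replace Bonferroni with Holm for whatever post-hoc family is used, and name that family.

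Alternatively, for each secondary outcome pre-name one contrast per arm pair (the month-12 difference or the slope to 12 months). Test the matching 2-df between-arm hypothesis at two-sided 0.05 and, only if it is significant, test the three pairs at 0.05 each. Keep Holm for any tests across several visits.

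The cost is one sentence and no new data. Confidence intervals no longer correspond one to one with the tests, and the error rate on a truly null pair rises from 1.7% to at most 5%. Familywise error is held at 5% within each outcome but not across outcomes; the plan should say so.

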Secondary outcomes are designed to capture additional dimensions of therapeutic impact, including disease progression, neuromuscular performance, respiratory function, and patient-reported quality of life. Longitudinal changes in ALSFRS-R across all follow-up visits will provide an index of disease trajectory. Limb function will be evaluated using the Manual Muscle Test (MMT) to assess muscle strength and the Modified Ashworth Scale (MAS) to quantify spasticity. Respiratory function will be assessed using forced vital capacity (FVC), vital capacity (VC), forced expiratory volume in 1 second (FEV1), the FEV1/FVC ratio, peak expiratory flow (PEF), and maximal voluntary ventilation (MVV), standardized to predicted values based on age, sex, and height. Quality of life will be measured using the ALS Assessment Questionnaire-40 (ALSAQ-40), which covers physical mobility, activities of daily living, emotional well-being, and social engagement. Fiberoptic Endoscopic Evaluation of Swallowing (FEES) will be used as the primary method for evaluating swallowing function. FEES is a validated, gold-standard tool that allows real-time visualization of the pharyngeal phase of swallowing. FEES will be used for baseline assessment and regular follow-up evaluations. This will enable us to track the progression of swallowing dysfunction throughout the course of ALS and assess the impact of the intervention on bulbar function. In the nested imaging substudy, presynaptic integrity will be evaluated using ^18^F SynVesT-1 PET at baseline and Month 6, with standardized uptake value ratios (SUVR) in motor system regions serving as mechanistic biomarkers. Exploratory analyses will also examine correlations between synaptic PET changes and clinical measures (ALSFRS-R, respiratory outcomes, MMT, MAS, and ALSAQ-40).

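### The exploratory PET–clinical correlations name no adjustment for randomised arm; if pooled over arms, they can show a synaptic link that no arm contains

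*Protocol article*

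**What the plan says.** Section 3.8 (Statistical analysis) states the method for the imaging–clinical link in one sentence: "Correlations between imaging and clinical outcomes will be examined using Pearson or Spearman coefficients depending on distribution". Distribution is the only stated basis for choosing between the coefficients. Neither coefficient takes covariates, and the sentence does not say whether the arms are pooled, taken separately or adjusted for.

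Section 3.6 (Outcome measurement) gives the status and the variables: "Exploratory analyses will also examine correlations between synaptic PET changes and clinical measures". PET therefore enters as a change score, and since "presynaptic integrity will be evaluated using ^18^F SynVesT-1 PET at baseline and Month 6", that change covers six months.

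The neighbouring analyses do carry arm and baseline. The primary model is described as "including group, time, and group × time interaction, with baseline score as covariate", and for the imaging outcome "changes in SV2A PET SUVR values will be analyzed using the same mixed-effects framework, with multiplicity controlled across primary regions of interest".

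Section 2 (Objectives and hypothesis) says what the link is meant to support: "these clinical benefits may be linked to measurable synaptic changes, providing mechanistic evidence for Tuina as a complementary therapy in ALS". The closing part of the abstract likewise expects the findings to tie gains in function to what happens at the synapse.

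**The concern.** The design has three randomised arms: "Eligible participants will be randomly assigned in a 1:1:1 ratio to one of three groups". A coefficient computed over all patients combines two things: how patients within an arm vary together, and how the arm means differ. Only the first tells us whether patients who keep more synaptic signal also keep more function. The second restates the two treatment effects.

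The trial hopes that Tuina moves both SUVR and function. In exactly that case a pooled coefficient is pushed away from zero, even if synaptic change says nothing about functional change within any arm. These correlations are the only stated analysis that joins the two measurements. A positive result could therefore be reported as a patient-level synaptic link when it only reflects two separate group effects.

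**Working it through.** **1. The plan's own figures.** Section 3.2 uses an F-test with three groups, f = 0.35, α = 0.05 and 90% power. With a noncentral F and λ = N·f², power is 0.896 at N = 105 and 0.9047 at N = 108. So 108 is the smallest multiple of three that reaches 90%, and the stated 0.905 is reproduced. With 20% dropout, 36/0.8 = 45 per arm, or 135 in all. These figures are correct. The plan gives no effect size for PET and no figure for the correlations.

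**2. Inputs to the check.**
- From the plan: three equal arms; f = 0.35 for ALSFRS-R.
- Assumed: the same f applies to six-month clinical change (the plan's primary comparison is the slope to 12 months); PET f of 0.35, with 0.5 and 0.7 as alternatives; only the Tuina arm shifted; 30 to 135 patients scanned; zero correlation within every arm.

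With one arm shifted, f = d·√2/3, so f = 0.35 means d = 0.35 × 3/√2 = 0.742 SD.

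**3. Pooled correlation created by the arms alone.**

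ρ = f_PET·f_clin / √[(1 + f_PET²)(1 + f_clin²)]

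With 0.35 for both: ρ = 0.1225/1.1225 = 0.109.

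**4. How often a nominal two-sided 5% test rejects** (simulation, 10,000 trials per setting). The pooled test uses N − 2 degrees of freedom; the partial correlation given arm uses N − 4. Entries are pooled Pearson, with the arm-adjusted test in brackets.

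| PET f / clinical f | N = 30 | N = 60 | N = 108 | N = 135 |
|---|---|---|---|---|
| 0.35 / 0 | 5.3% (5.2%) | 5.3% (5.2%) | 5.3% (5.3%) | 4.7% (4.8%) |
| 0.35 / 0.35 | 8.9% (5.0%) | 12.7% (4.9%) | 20.1% (4.9%) | 24.6% (4.6%) |
| 0.5 / 0.35 | 12.5% (5.3%) | 20.0% (5.2%) | 33.4% (4.6%) | 41.1% (5.7%) |
| 0.7 / 0.35 | 17.4% (5.3%) | 30.5% (5.0%) | 51.3% (4.7%) | 60.7% (5.1%) |

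Spearman behaves the same way: at 0.35 / 0.35 it rejects in 8.5%, 12.5%, 19.2% and 23.7% of trials. Choosing the coefficient by distribution does not help. The first row shows that an effect on PET alone causes no inflation.

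**5. Baseline, a separate route.** If PET change and clinical change each correlate with baseline severity by r₁ and r₂ and are otherwise unrelated, the induced correlation is r₁·r₂. With 0.3 for both (assumed) it is 0.09; with 0.5 it is 0.25. By Fisher's z at N = 135, a 5% test rejects in about 18% and 83% of trials. This correlation lies inside the arms, so adjusting for arm does not remove it, and taking PET as a change score does not remove it by itself.

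**The case against.** The strongest reply is that the problem is read from silence. The sentence does not say that the arms are pooled, and by-arm or partial coefficients could be set out in an analysis plan that is not shown. That stands: a reader might infer that the protocol commits to an unadjusted pooled analysis, and the text does not go so far. What remains is that the article names a specific method, gives distribution as its only condition, and puts it beside models that spell out group and baseline.

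Second, a reader might infer that the whole mechanistic objective hangs on these coefficients. It does not. The mixed model for SUVR change compares the arms directly and addresses whether clinical benefit is accompanied by preserved synaptic signal. The Discussion and Conclusion credit the PET substudy as a whole, without mentioning the correlations.

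Third, the analysis is labelled exploratory, section 3.8 attaches its 0.05 threshold to primary analyses, and r = 0.109 is only about 1% of shared variance (0.109² = 0.012). All true. The rejection rates illustrate how easily a link could appear; they are not error rates for a test the plan has declared.

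Fourth, inflation needs a real effect on both measures, in which case two randomised effects exist and the error is confined to the patient-level reading. That also stands, and it sets the limit of the point.

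Finally, a reader might fault the absence of multiplicity control over all measures and regions. For an exploratory analysis that is optional and no part of this point.

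**Conclusion.** The point holds as a low-cost improvement to an exploratory analysis. If the coefficients are pooled and Tuina shifts both SUVR and function, arm differences alone give a pooled r of about 0.11 at f = 0.35 on both, and a nominal 5% test rejects in about 9% (N = 30) to 25% (N = 135) of trials with no within-arm association. Larger assumed PET effects raise this. Adjustment for arm brings it back to about 5%, and with an effect on PET alone the inflation does not arise.

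The size rests on assumptions that the document does not supply: the PET effect, the number scanned, the carry-over of f to six-month clinical change, and a shift in the Tuina arm only. Shared dependence on baseline severity is a second and distinct source of correlation. It acts within arms, so it should not be offered as evidence for the arm artefact.

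The primary ALSFRS-R conclusion and the randomised comparison of SUVR are unaffected. The point matters because the abstract and section 2 present the link as mechanistic.

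**What to change.** In section 3.8, replace the correlation sentence. Estimate the association between six-month SUVR change and six-month clinical change by linear or rank-based regression, reported as a partial correlation, adjusted for randomised arm, baseline clinical score and baseline SUVR. Show the by-arm estimates beside it. State that the result is an association and does not prove mediation; even the adjusted estimate cannot do that.

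The cost is one sentence, a few lines of code and about four degrees of freedom (two for arm, one for each baseline). No new data are needed. Section 3.1 says recruitment is ongoing, so the change can be recorded before analysis.
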